# Intralesional steroid injections to prevent refractory strictures in patients with oesophageal atresia: study protocol for an international, multicentre randomised controlled trial (STEPS-EA trial)

**DOI:** 10.1136/bmjopen-2019-033030

**Published:** 2019-12-16

**Keywords:** oesophageal atresia, intralesional steroid injections, anastomotic strictures

## Abstract

**Introduction:**

Anastomotic stricture formation is the most common postoperative complication after oesophageal atresia (OA) repair. The standard of care is endoscopic dilatation. A possible adjuvant treatment is intralesional steroid injection, which is thought to inhibit scar tissue formation and thereby to prevent stricture recurrence. We hypothesise that this intervention could prevent refractory strictures and reduce the total number of dilatations needed in these children.

**Methods and analysis:**

This is an international multicentre randomised controlled trial. Children with OA type C (n=110) will be randomised into intralesional steroid injection followed by balloon dilatation or dilatation only. Randomisation and intervention will take place when a third dilatation is performed. The indication for dilatation will be confirmed with an oesophagram. One radiologist—blinded for randomisation—will review all oesophagrams. The primary outcome parameter is the total number of dilatations needed with <28 days’ interval, which will be analysed with a linear-by-linear χ^2^ association test. Secondary outcome parameters include the level of dysphagia, the luminal oesophageal diameter and stricture length (measured on the oesophagrams), the influence of comedication on stricture formation, systemic effects of intralesional steroids (cortisol levels, length and weight) and the cost-effectiveness. Patients will undergo a second oesophagram; length and weight will be measured repeatedly; a scalp hair sample will be collected; and three questionnaires will be administered. The follow-up period will be 6 months, with evaluation at 2–3 weeks, 3 and 6 months after the intervention.

**Ethics and dissemination:**

Patients will be included after written parental informed consent. The risks and burden associated with this trial are minimal. The institutional review board of the Erasmus Medical Centre approved this protocol (MEC-2018–1586/NL65364.078.18). The results of the trial will be published in a peer-reviewed scientific journal and will be presented at international conferences.

**Trial registration numbers:**

2018-002863-24 and NTR7726/NL7484.

Strengths and limitations of this studyThis is the first prospective study investigating the effectiveness of intralesional steroid injection combined with endoscopic dilatation for the treatment of recurrent oesophageal strictures in children operated on for oesophageal atresia (OA).The determination of long-term cortisol levels over a period of 3 months will give objective information on possible systemic effects of intralesional steroid injection in children with OA.Besides the effectiveness and safety of intralesional steroid injection, cost-effectiveness of this treatment will be evaluated.The rarity of the disease makes patient recruitment challenging.

## Introduction

Oesophageal atresia (OA) is a congenital malformation which can present with or without a tracheoesophageal fistula, with a European prevalence of 2.43 cases per 10 000 births.^1 2^ With better treatments, survival rates have increased to over 90%.^1 3 4^ Still, anastomotic stricture formation remains the most frequent postoperative complication in up to 60% of cases.^5^ Especially refractory strictures form a great burden for both patients and their parents.

The incidence of refractory strictures is poorly reported due to the variety in definitions used in literature. Regarded as a consensus among experts, the European Society for Paediatric Gastroenterology Hepatology and Nutrition (ESPGHAN) has set the following definition for a refractory oesophageal stricture: an anatomical restriction without endoscopic inflammation that results in dysphagia after a minimum of five dilatation procedures at maximally 4-week intervals.^6 7^

Recently, the Dutch Consortium for Esophageal Atresia (DCEA) conducted a retrospective multicentre study in the Netherlands to assess risk factors for stricture formation in children with OA. The study population consisted of 436 children born with OA between 1999 and 2013 with an end-to-end oesophageal anastomosis. Thirty-two (7.3%) of them required ≥5 dilatations within an interval of 28 days.^5^

The initial treatment of an anastomotic stricture consists of endoscopic dilatation, either balloon dilatation or semirigid dilatation.^6^ Consensus on the preferred technique has not yet been established. A refractory stricture requires multiple dilatations under general anaesthesia, for which the child needs to be hospitalised. This adds significantly to the burden of the disease. It is therefore important to minimise the occurrence of refractory strictures and with that the need for dilatations.

In a recent ESPGHAN guideline, various adjuvant treatments are mentioned, for example, intralesional or systemic steroids, topical mitomycin C, oesophageal stents and surgical resection. Our trial will focus on intralesional steroid injections since we as well as the other centres involved in this trial have had successful results with this treatment in several patients.^8^

The literature on intralesional steroid injection in children with OA is scarce, but promising results have been described in both children and adults with all types of oesophageal strictures (table 1). Most studies are outdated case reports or series.^9–14^ Four relatively recent randomised controlled trials (RCTs) on this topic included only adults with underlying diagnoses other than OA, like caustic strictures after acid ingestion, peptic strictures and anastomotic strictures after oesophagectomy with gastric tube reconstruction.^15–18^ Reported beneficial effects were reduction of dilatation procedures,^16^ longer intervals between dilatation procedures,^17^ improvement of luminal diameter^15^ and relief of dysphagia.^18^

**Table 1 T1:** Summary of literature on clinical findings on intralesional steroid injections for oesophageal strictures, including retrospective cohort studies in children <12 years (range 0–14 years)

Author (year)	Type of study	Characteristics	Main outcomes
Camargo *et al* (2003)^15^	Double-blind RCT	14 adult patients, corrosive strictures	No significant difference in dilatation frequency and dysphagia. Significant improvement in obtained diameter (p<0.05). No adverse events reported.
Ramage *et al* (2005)^16^	Double-blind RCT	30 adult patients, peptic strictures	Less patients required repeat dilatation in the steroid group (13% vs 60%, p=0.0209). Shorter time to repeat dilatation in the control group (p=0.01). No adverse events reported.
Hirdes *et al* (2013)^17^	Double-blind RCT	60 adult patients, anastomotic strictures after oesophagectomy with gastric tube reconstruction	No significant decrease in frequency of repeat dilatation or prolongation of dysphagia-free period. Four patients developed *Candida* oesophagitis.
Pereira-Lima *et al* (2015)^18^	Double-blind RCT	19 adult patients, anastomotic strictures after oesophagectomy with gastric tube reconstruction	Significant improvement on dysphagia at 1 and 6 months (p=0.021 and p=0.009). No perforation or haemorrhage of oesophageal candidiasis, no other adverse events reported.
Kochhar and Makharia (2002)^35^	Prospective	71 patients (13–78 year), all kinds of strictures	Periodic dilatation index decreased significantly after injection (p<0.001). No adverse events reported.
Nijhawan *et al* (2016)^36^	Prospective	11 adult patients, corrosive strictures	Significant improvement of maximum dilatation (p<0.001) and number of dilatations per month (p<0.001). No adverse events reported.
Divarci *et al* (2016)^19^	Retrospective	32 children (mean age 3.6 years), corrosive strictures	Mean number of dilatation sessions was decreased (p=0.003). Mean frequency of dilatations in weeks extended (p<0.001). Only a positive effect in short-segment strictures (<3 cm, 92% of patients dysphagia-free). No serious adverse events reported, one transient cushingoid phenotype but no real adrenal suppression.
Cakmak *et al* (2016)^20^	Retrospective	38 children (median age 1.5 years), OA (n=19) and corrosive strictures (n=19)	No significant difference in treatment effectiveness between steroid injection and others (p>0.05). Intralesional steroid injections performed only in patients with long (>5 cm) and corrosive strictures and ≥5 dilatations. Four patients with oesophageal perforation at other dilatation sessions than the intralesional steroid injection.

OA, oesophageal atresia; RCT, randomised controlled trial.

In children, only retrospective studies have been performed, which mostly included caustic strictures.^19 20^ Divarci *et al* analysed data of 32 children with corrosive strictures with a mean age of 3.6 years (±2.5 years); after the intervention, the number of dilatations had significantly decreased and the intervals between dilatations had extended.^19^ Cakmak *et al* included 38 children with either OA or corrosive strictures with a median age of 1.5 years (range 0–14 years)^20^ but did not find a significant difference in treatment effectiveness. None of the above-mentioned studies reported any systemic effects of the local intralesional steroid injections.

All studies used triamcinolone acetonide (TAC). The exact mechanism by which TAC enhances the efficacy of dilatation is unclear. It has been proven very effective in the treatment of hypertrophic scars of the skin and keloid. A recurring anastomotic stricture can be seen as a hypertrophic lesion. The injected TAC inhibits collagen formation, enhances collagen breakdown, decreases fibrotic healing that occurs after dilatation and prevents cross-linking of collagen that causes contractions in scar tissue.^21 22^

The recurrent dilatations and readmissions impose a substantial burden on the healthcare system. To date, there is no evidence on the cost-effectiveness of intralesional steroid injections. However, in the current era of evidence-based and cost-effective medicine, proof of cost-effectiveness is highly relevant.

The primary objective was to evaluate whether intralesional steroid injections combined with endoscopic dilatation can prevent refractory strictures in children with OA and recurrent oesophageal stenosis, and thus can minimise the number of dilatations needed with a 28 days’ interval between the dilatations.

The secondary objectives were

To compare the level of dysphagia and the child’s eating behaviour between the two groups.To compare the effect of intralesional steroid injections on the luminal diameter and the stricture length between the two groups.To evaluate a possible influence of comedication (eg, antacids) on stricture formation.To analyse the possible systemic effects of a one-time intralesional steroid injection.To analyse the cost-effectiveness of the use of intralesional steroid injections to prevent refractory strictures.

## Methods and analysis

The STEPS-EA trial is an international, multicentre, single-blinded RCT with a 1:1 randomisation to injection with 10 mg/mL TAC (Kenacort-A 10) prior to balloon dilatation and balloon dilatation without any injection. The participating centres are tertiary (academic) hospitals that collaborate within the European Reference Network on Inherited and Congenital Abnormalities (ERNICA, ern-ernica.eu) and that routinely provide care for children with OA.

### Patient and public involvement

Parents of patients were involved in the end stage of the design of the trial. We presented our plans for the trial to a DCEA meeting in which also representatives of the patients’ association Vereniging voor Ouderen en Kinderen met een Slokdarmafsluiting (VOKS) took part. They were invited to comment on the study design, intervention or time required to participate in this trial. Consensus was reached on the final design during this meeting. The patients’ association will not be involved in the recruitment and conduct of the trial. We will involve them in dissemination, however, by presenting the trial results at a members’ day or in their monthly newsletter. As the VOKS is a member of the European Federation of Esophageal Atresia and Tracheoesophageal fistula Support Groups E.V., patients and parents throughout Europe will be informed about the results.

### Participants

OA can be a very heterogeneous disease. About 90% of the children with OA has type C.^5 23^ In order to make the two treatment groups as equal as possible, only children with OA type C who underwent surgery with primary anastomosis within the first days of life and who developed a recurrent oesophageal stricture will be eligible. Children will be included if they are ≥3 months old at the time of the intervention and in need of a third dilatation. Written parental informed consent will be obtained by the local principal investigator (PI) or another member of the local research team. Exclusion criteria are lack of parental consent or an impossibility—known from previous dilatations—to use an endoscope with a large enough diameter working channel to pass the endoscopic injector.

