### Recruitment

Patients will be recruited from hospitals in various European countries. Up until now, hospitals in Denmark, UK, Finland, France, Italy and Sweden have agreed to participate. During the inclusion period, it will remain possible for other centres to join. To achieve adequate participant enrolment, we have minimalised the exclusion criteria. Collaboration within ERNICA should make patient accrual achievable despite the rarity of the disease.

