**Figure 1 F1:**
[figure not shown]
Flowchart of the study design. Bold with underline indicates study procedures; the rest is standard of care. AP, anterior–posterior; iPCQ, iMTA Productivity Cost Questionnaire; MFS, Montreal Feeding Scale; OA, oesophageal atresia.

Prior to the balloon dilatation, an endoscopic needle (DVI-23-MH varices injector or equivalent) is prefilled with 1 mL Kenacort-A 10 and passed through the endoscope. Under direct vision, 0.25 mL will be injected in each of the four quadrants of the circular stricture. After the injection needle has been retracted from the working channel and good visualisation has been re-established, balloon dilatation will be performed up to the desired diameter. The balloon will remain insufflated for 1 min.

During a follow-up period of 6 months, patients will not receive any (additional) steroid injections, only balloon dilatations if needed. Meaning, patients in the steroid group will only receive one injection, and patients in the control group will receive no injections at all. After the study period has ended, treatment is again free of choice.

Two to 3 weeks after the dilatation procedure, a second oesophagram will be made in children in both study groups. All oesophagrams will be reviewed by one specialised paediatric radiologist of the coordinating hospital, who will determine the oesophageal diameter and stricture length. Earlier studies have proven that these measurements can be obtained from an oesophagram.^24^ The parents will be informed about the results and the normal standard of care will be continued.

Each patient will be followed up for 6 months after the third dilatation, with recording of possible side effects, complications and additional dilatations. Length and weight will be measured at 2–3 weeks, 3 and 6 months after the third dilatation. In the context of the cost-effectiveness analysis, the parents will be asked to fill out a modified version of the iMTA Productivity Cost Questionnaire (iPCQ)^25^ at 3 months after the third dilatation.

At evaluation at 6 months, we will collect a scalp hair sample from the child to determine long-term cortisone and cortisol levels.^26 27^ The hair locks will be stored for final batch analysis. Lastly, the parents will be asked to fill out the Montreal Feeding Scale (MFS)^28–30^ and again the iPCQ. After this, the study period will end.

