### Data collection

All participating centres are familiar with the procedure of injecting Kenacort-A 10 in the lesion via an injection needle through the endoscope. However, to guarantee equality of the intervention, the relevant practitioners in all centres will be trained by the PI of the trial. Radiological interobserver variability will be avoided by having all oesophagrams reviewed by one radiologist.

The internationally validated MFS^28–30^ will be used to measure dysphagia. The MFS has often been used in previous research in children with OA. The scalp hair sample will be taken from the posterior vertex; cortisol levels will be determined with the liquid chromatography–tandem mass spectrometry method for quantification of steroids.^26^

The cost-effectiveness analysis will follow established methods for economic evaluations and costing studies in healthcare.^31 32^ Both medical and non-medical costs will be collected. Medical costs will include costs of surgeries (dilatations), steroid injections, hospital days (on the ward or the intensive care unit), medication (such as analgesics) and diagnostic radiography. Costs of healthcare provided by others than the participating centres (such as other hospitals or general practitioners) will be ignored in this study, as these are unlikely to be affected by the intervention. Non-medical costs will include costs of special diets, costs related to hospital visits and productivity losses related to both paid and unpaid works. The non-medical costs will be measured using the iPCQ,^25^ supplemented with additional questions on costs of special diets and costs related to the child’s hospitalisation. The original iPCQ questions are validated in English. The complete questionnaire including the additional questions will be translated to the languages required for this trial using the forward–backward translation method, as will the MFS for the languages it has not been validated for.

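### The exclusion list does not cover intralesional steroid given at the first or second dilatation, which dilutes the contrast and blurs the objective on a one-time injection

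*Protocol article*

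**What the plan says.** Participants limits entry to type C atresia with early primary anastomosis and a recurrent stricture, and adds: "Children will be included if they are ≥3 months old at the time of the intervention and in need of a third dilatation". The exclusions follow as a closed list: "Exclusion criteria are lack of parental consent or an impossibility—known from previous dilatations—to use an endoscope with a large enough diameter working channel". The second item concerns access for the injection needle. Recruitment explains why the list is short: "To achieve adequate participant enrolment, we have minimalised the exclusion criteria". Neither section mentions treatment given at the first two dilatations.

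The treatment under test is not new to the sites. The Introduction gives experience as the reason for choosing it: "since we as well as the other centres involved in this trial have had successful results with this treatment in several patients". Data collection adds: "All participating centres are familiar with the procedure of injecting Kenacort-A 10 in the lesion via an injection needle through the endoscope".

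On exposure during the trial, Patient timeline says: "patients in the steroid group will only receive one injection, and patients in the control group will receive no injections at all". Investigational product rules out a second injection for anyone in the study period, which Outcome parameters starts on the day of the third dilatation. One secondary objective reads: "To analyse the possible systemic effects of a one-time intralesional steroid injection".

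**The concern.** Eligibility is fixed in the protocol and is not something an analysis plan can settle later. As written, a child injected at the second dilatation who then needs a third can be randomised to either arm.

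- **Control arm.** The child counts as untreated but has had the study treatment, possibly only weeks before.
- **Steroid arm.** The trial injection is a repeat. This sits badly with the rule against a second injection, because the trial injection falls on the first day of the study period.

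Two things are at stake. The first is the size of the contrast on which 52 per group was calculated. The second is the meaning of the systemic-effect outcomes. Hair cortisol is averaged over the 3 months after the third dilatation, and growth is measured from that dilatation. Benefits and risk assessment describes the product as slow-release, so an injection at the second dilatation could still contribute in that window. How long it would do so is not stated.

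**Working it through.** **1. What the text admits.** Each entry condition was checked against a child with a steroid injection at dilatation 2.

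| Condition (Participants) | Bars the child? |
|---|---|
| Type C, early primary anastomosis, recurrent stricture | No |
| At least 3 months old, needs a third dilatation | No |
| Parental consent given | No |
| Working channel large enough | No |

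The restrictions on injections in Patient timeline and Investigational product apply from the third dilatation onwards, so they do not close the gap.

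**2. Reproducing the planned sample size.** Inputs from Sample size calculation and Table 2:

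- control frequencies 4, 7, 9, 7, 16 and 10 out of 53
- steroid frequencies 0.142, 0.302, 0.170, 0.160, 0.132 and 0.094
- two-sided alpha 0.05, target power 80%, 52 per group

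The linear-by-linear statistic is M² = (N − 1)r², referred to 3.84. Here r is the correlation between arm and category score. The article does not give the scores, so two sets were simulated with 100,000 runs each:

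- scores 1 to 6: power 0.822 at 52 per group
- scores 3, 4, 5, 6, 8.5 and 12 (the last two assumed): power 0.789 at 52 per group

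The smallest simulated n per group reaching 80% was about 50 and 54 respectively. The stated 52 is therefore reproduced, and no figure in the plan is shown to be wrong.

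**3. Illustrating dilution.** Assume that a share f of controls has full carry-over and follows the steroid column, while the steroid arm is unchanged:

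control mix = (1 − f) × control column + f × steroid column

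With scores 1 to 6, the control mean is (4 + 14 + 27 + 28 + 80 + 60)/53 = 213/53 = 4.019. The steroid mean is 0.142 + 0.604 + 0.510 + 0.640 + 0.660 + 0.564 = 3.120. The difference is 0.899, and it shrinks by the factor 1 − f.

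| f (assumed) | Mean difference | Simulated power, 52 per group |
|---|---|---|
| 0 | 0.899 | 0.82 |
| 0.05 | 0.854 | 0.78 |
| 0.10 | 0.809 | 0.73 |
| 0.20 | 0.719 | 0.63 |

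**4. The opposite mechanism.** Pre-treated children might instead be non-responders. If a share f of the steroid arm follows the control column and controls are unchanged, the simulated power is again about 0.78, 0.73 and 0.63. Either mechanism dilutes the contrast to a similar degree.

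The documents give no value for f. The table shows sensitivity to f and is not an estimate of the loss.

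**The case against.** Several points on the other side are sound.

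- **The arms are defined within the study period.** A reader might infer that the arms are not what the objectives state. The documents do not support that. The statement on one injection or none explains a sentence about the 6-month follow-up. The primary objective defines neither a never-injected control nor a first-ever injection, and only one secondary objective says one-time. The contrast allocated at the third dilatation is as described.
- **There is no bias between arms.** A reader might also infer a biased comparison. Randomisation, stratified by centre, balances earlier exposure in expectation. The between-arm differences in cortisol and growth still estimate the effect of adding one injection, in a partly pre-treated population.
- **Early use is not documented.** The article reports success in several patients, without timing. The one paediatric series in Table 1 that includes atresia used injection only in long, corrosive strictures after at least five dilatations, which points to late use.
- **The power figures are an extreme case.** Full carry-over in controls is hard to square with a child who needed a third dilatation despite an injection. The shares are assumed.
- **Broad entry is deliberate**, because the disease is rare.

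These points limit the size of the problem and the wording of the conclusion. They do not remove the gap: the list is presented as complete, the sites use the treatment, and nothing says whether pre-treated children belong in the trial. A reader might want the exclusion widened to systemic steroids, mitomycin C, stents and resection. The Introduction names these as guideline options but does not report early use of them at the trial sites, so the documents do not support that step.

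**Conclusion.** The point holds as a gap in eligibility. A child already injected with steroid at the first or second dilatation can enter either arm. The consequences are dilution of the treatment contrast and a less clear reading of the systemic-effect objective, together with an awkward fit with the rule against a second injection.

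The size is unknown because prior use is not quantified. Under full carry-over in controls and scores 1 to 6, 10% pre-treated controls would take power from about 82% to about 73%. With rare prior use the loss is negligible. The allowance from 104 to 110 patients is meant for dropout and missing data, so it was not set aside for dilution. The conclusion rests on reading the exclusion list in Participants as complete, which is how the article presents it. The correction is worth making because it is cheap.

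**What to change.** Add one exclusion to Participants: any intralesional steroid injection at the anastomosis before randomisation. Add a matching item to the screening form. Record other earlier adjuvant treatment of the stricture as a baseline variable, so that its frequency can be reported by arm.

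The cost is one line of protocol text, two form fields and an amendment. The downside is the loss of the few children already injected, which runs against the stated wish to keep exclusions minimal. If such children are rare, few are lost. If they are common, the dilution shown above is a stronger reason to exclude them, and the effect on accrual should then be checked with the sites.
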